### Strategies to improve adherence to interventions {11c}

Adherence to interventions will be improved by means of the following strategies:Prior to study protocol initiation, an investigator meeting will be held in each center to detail the study protocol and encourage the staff to adhere to it;The enrolling centers will be selected according to a similar protocol on NIV interface rotation (i.e., in case of the occurrence of a new pressure ulcer or patient discomfort) that represents a common standard of care.

To monitor the adherence to the study protocol, the effective time of ventilation derived from the ventilator counter, the exact time of interface change, and the adherence to the skincare bundle protocol will be recorded as well.

### Relevant concomitant care permitted or prohibited during the trial {11d}

In both arms, diagnostic tests, administration of systemic therapy (e.g., antibiotics, steroids, and inhaled bronchodilators), and hemodynamic management will be performed according to the best clinical practice at enrolling centers. The right size of the mask will be selected according to the indications provided by the manufacturer. The mask straps will be adjusted in compliance with the “two-finger rule” so as to not tighten too hard the headgear [37].

In accordance with international guidelines [1], patients needing NIV to avoid or as an alternative to invasive ventilation will receive NIV for as long as possible during the first 24 h and thereafter until the acute cause is resolved, typically after about 2 to 3 days. NIV will be started when pH < 7.35 and PaCO_2_ > 45 mmHg persist or develop despite optimal medical therapy, targeting an oxygen saturation of 88–92%. Blood gas exchange will be performed before starting NIV treatment, 2 h after NIV institution, and thereafter, when clinically indicated. NIV will be initially set to pressure support mode with a ventilator designed specifically to deliver NIV or with an ICU ventilator equipped with an NIV mode. Positive end-expiratory pressure (PEEP) will be set at 3–5 cmH_2_O, while inspiratory pressure support (PS) will be titrated to achieve adequate augmentation of chest/abdomen movement with an expiratory tidal volume of 6-8 ml/kg and a reduction of respiratory rate (< 30 breaths/min). A good patient-ventilator interaction will be also assessed by checking pressure-flow curve monitoring and the patient’s respiratory pattern. The presence of active humidification will be left to the choice of the patient’s attending physician, although heated humidification should be considered if the patient complains of mucosal dryness or if respiratory secretions are thick and tenacious. The weaning strategy will be documented in the medical and nursing records. The following suggested protocol will be given as a general indication for weaning: continue NIV for 16 h on day 2; 12 h on day 3, including 6–8 h overnight use; NIV may be discontinued on day 4 unless continuation is clinically indicated [26]. The suggested monitoring during NIV will be continuous peripheral oxygen saturation, intermittent measurement of PaCO_2_ and pH, and ECG monitoring in patients with a pulse rate > 120 bpm or with dysrhythmia or possible cardiomyopathy. As the international guidelines recommend keeping the skin in contact with the medical equipment dry and clean, a skincare bundle protocol will be adopted by all centers. If a patient needs prolonged continuous NIV, brakes will be programmed and annotated in the case report form (CRF). In case of instability, the interface will be removed for about 10 min solely to ensure oxygenation [38]. In both groups, when signs of skin breakdown become apparent, strategies involving the application of different wound care dressings, regular breaks whenever possible, and/or rotation between the two interfaces will be implemented. In case of mask-related rash, even in the absence of allergy, topical steroids may be indicated and/or antibiotics if the wound becomes infected. If NIV causes severe gastric distension, a nasogastric tube may be placed.

For patients intubated due to hypercapnic ARF secondary to COPD or other causes related to hypercapnic ARF, NIV might be applied during early extubation and weaning. According to the international guidelines, NIV is recommended to aid weaning from invasive mechanical ventilation, when local expertise in its use exists [1, 14]. Patients receiving invasive mechanical ventilation will be treated according to the clinical guidelines [1]. After reaching maximum medical treatment, once the ventilation is set to controlled mode and pH and PaCO_2_ are normalized in the presence of neurological, hemodynamic, and respiratory stability, patients will be extubated and subjected to NIV. The ventilator will be initially set at the same PEEP and inspiratory PS level applied during invasive mechanical ventilation, setting it at the fastest pressure rise time. Successively, NIV setting will be titrated to maintain arterial blood gas in a normal range, a tidal volume between 6 and 8 ml/kg of predicted body weight, and a respiratory rate below 25 breaths/min. In patients tolerating spontaneous breathing. NIV will be gradually tapered off until they can permanently sustain spontaneous breathing.

### Provisions for post-trial care {30}

NIV is extensively used in clinical practice. All patients included in the study deserve NIV treatment according to their clinical symptoms and pathology. Major complications due to NIV treatment are not expected. If any complications occur, they will be treated according to the best clinical practice.

### Outcomes {12}

The primary effectiveness outcome is the proportion of patients developing at least one pressure sore of any stage at 36 h from randomization. The reason why this measure of effectiveness was chosen is that it is more clinically relevant than the overall number of pressure sores. Furthermore, 36 h seems to be an appropriate time point given that the time it takes for pressure sores to develop is extremely variable, but it might as well be very short.

Secondary outcomes will be the onset, number, and stage of pressure sores and comfort during NIV measured at different time points (12, 24, 36, 48, 60, 72, 84, 96 h). At the same time points, the location of pressure sores per patient will also be recorded, i.e., forehead, nose bridge, left cheek, right cheek, chin, left periauricular, right periauricular, and occipital. The study will also monitor the number of patients that interrupts NIV due to discomfort, the presence/absence of eye irritation in relation to both oronasal and full face/hybrid mask, poor adherence to the protocol (e.g., duration of NIV treatment/day, interfaces changed and hygiene protocol application both during each 12-h protocol period) and the presence/absence and types of vasoactive medications, i.e., epinephrine, norepinephrine, vasopressin, dobutamine, dopamine, other. Further outcomes include the costs for intervention implementation (e.g., mask-related costs) and those related to the care of pressure sores (antibiotic treatment, specialist medical visits).

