#### Exclusion criteria

Patients, on admission, with skin breakdown or non-blanchable erythema in one of the following areas: nasal bridge, nasolabial fold, cheek, or scalp;Patients who refuse to consent to the study protocol;Patient known to be pregnant;Patients with the following contraindications to NIV: lack of spontaneous breathing; gasping; anatomical or functional airway obstruction; gastrointestinal bleeding or ileus; coma; massive agitation; massive retention of secretions despite bronchoscopy and aggressive physiotherapy; hemodynamic instability (e.g., cardiogenic shock, myocardial infarction); status post-upper gastrointestinal surgery;Patients entering the hospital with asthma or cardiogenic pulmonary edema;Patients with tracheostomy;Patients receiving NIV only for palliation of symptoms (e.g., dyspnea relief). These patients belong to category 3 as defined by the Society of Critical Care Medicine (SCCM) Task Force assessing the palliative use of noninvasive positive pressure ventilation [35];Use of high-flow nasal cannula integrated with NIV to prevent reintubation;Pre-existing skin erythematosus disorders;Known hypersensitivity to skin protective devices (i.e., polyurethane films, colloids, foams);More than 2 h of NIV application before randomization;Patients already included in the study protocol at an earlier stage of their hospital stay; andRefuse to wear NIV interface due to comfort.

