### Intervention description {11a}

In the control group, mask will be chosen among the three types of masks available: oronasal, total face, or hybrid mask, according to the standard of care of the participating centers. Patients wearing oronasal masks will receive protective dressing on their nasal bridges before starting NIV. Interface will be changed in case of discomfort, referred by the patient as unbearable, or in the presence of a pressure sore.

In the intervention group, the mask initially applied to the patient will be randomly chosen between the two most used masks in that center among those available (i.e., oronasal, total face, or hybrid mask). Thereafter, NIV mask will be changed every 6 h, alternating the two different interfaces. Patients wearing oronasal masks will receive a protective dressing on the nasal bridge before starting NIV. In case of discomfort, referred by the patient as unbearable related to one of the two interfaces, NIV will be continued with the other mask.

In both arms, the treatment will be continued until patients require NIV according to the assigned protocol.

Prior to patient recruitment, the candidate assessors (doctors and nurses) will be trained to recognize and stage pressure sores through a specific standardized education module. At the end of this course, the trainees will be asked to take a final test where they have to correctly stage 10 pressure sores. Only those trainees able to identify and stage all 10 sores will be qualified as assessors. To minimize detection bias, assessors will not participate in patient care and will be blinded to treatment allocation.

The skin underneath the mask and occipital region will be inspected every 12 h for possible damage by the assessors. If a pressure sore is detected, the physician in charge of the patient will be promptly informed, and a note will be written on the nursing record. Pressure sores will be staged according to the classification of the National Pressure Ulcer Advisory Panel, European Pressure Ulcer Advisory Panel, and Pan Pacific Pressure Injury Alliance [36] (Table 1).

**Table 1 Tab1:** Pressure sores classification according to the classification of the National Pressure Ulcer Advisory Panel, European Pressure Ulcer Advisory Panel, and Pan Pacific Pressure Injury Alliance

Stage I	A reddened, painful area on the skin that does not turn white when pressed. This is a sign that a pressure ulcer may be forming. The skin may be warm, cool, firm, or soft.

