### Sample size {14}

Given a type I error of 0.05, a power of 0.8, an expected proportion of patients who develop pressure sores in the control group of 23% [39], and an expected dropout rate of 5%, 239 subjects per group are estimated to identify a 10% absolute difference in the proportion of patients developing pressure sores between intervention and control groups measured at 36 h from randomization.

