## Statistical methods

### Statistical methods for primary and secondary outcomes {20a}

The analysis will be performed according to the intention-to-treat (ITT) principle. Descriptive statistics will be calculated to summarize patient characteristics collected at study entry according to the randomization group. Categorical variables will be reported as absolute frequencies and percentages. Continuous variables will be represented as mean and standard deviation or median first and third quartiles if not normally distributed according to the Shapiro–Wilk test.

The raw risk of pressure sore will be calculated at each time point as the ratio between the number of subjects who developed a pressure sore at a given time point divided by the number of subjects undergoing NIV at that time point. Patients having a planned break at the time point considered, but not weaned off NIV, will be considered as patients undergoing NIV.

Mixed effect logistic regression models will be used to estimate the risk of pressure sores and the difference between interfaces, including a random intercept to account for clustering of the subjects within the center and repeated measures within patients. The response variable will be the presence/absence of pressure sores, whereas the independent variables will be the treatment, time (12, 24, 36, 48, 60, 72, 84, 96 h), and their interaction. The marginal predicted probabilities estimated by the model will provide the incidence of pressure sores at different times as well as overall. The inclusion of time as a covariate will allow to test the presence of a time trend in the incidence of pressure sores and to investigate the variation of time trends according to treatment group.

If the descriptive statistics will detect unbalanced characteristics between randomization groups (e.g., indication for NIV), the corresponding variables will be added as covariates in the logistic regression model.

Regarding the number of pressure sores, different mixed effect Poisson regression models will be applied: one for each time point to estimate the average number of pressure sores at each time point and a model in which only the highest number of pressure sores will be considered for each patient. Time will be included as offset to evaluate the average number of pressure sores per day.

The grade and location of pressure sores will be summarized using descriptive statistics at each time point.

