### Interim analyses {21b}

A single interim analysis will be performed when two-thirds of the predefined sample are randomized and completed the study. Early stopping criteria will be a predetermined 2-sided *p*-value < 0.01 for the rejection of the null hypothesis that the strategies are equivalent in terms of pressure sore incidence rate.

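### Stage I redness counts fully in the primary outcome, and no planned between-arm analysis separates it from established sores, although the trial says it will determine an effect on severity

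*Protocol article*

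**What the plan says.** - **Primary outcome (Outcomes {12}).** "The primary effectiveness outcome is the proportion of patients developing at least one pressure sore of any stage at 36 h from randomization".
- **Lowest stage (Intervention description {11a}, Table 1).** Stage I is a reddened, painful area that does not blanch. The table adds: "This is a sign that a pressure ulcer may be forming".
- **Entry (Exclusion criteria).** Patients are excluded if they present "with skin breakdown or non-blanchable erythema in one of the following areas", and four areas are then listed. Entry and the lowest outcome stage therefore turn on nearly the same sign. They are not identical: Table 1 adds pain, and the outcome sites also include forehead, chin and periauricular skin.
- **Inspections ({11a}, Participant timeline {13}).** Skin is inspected every 12 h for 4 days. Assessors take no part in care, are blinded to allocation, and must stage 10 of 10 test sores correctly. The article describes no repeat look or second assessor.
- **Analysis ({20a}).** The logistic model takes presence or absence of sores as its response, and the Poisson models count sores. The modified intention-to-treat analysis changes only the population. The cost-effectiveness ratio uses the proportion with sores, and comfort. On stage: "The grade and location of pressure sores will be summarized using descriptive statistics at each time point".
- **Stated aim.** Stage is a secondary outcome at eight time points ({12}). The discussion part of the abstract says the trial will determine whether rotation lowers severity as well as incidence and number.

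**The concern.** In every planned comparison of sores, one stage I call weighs the same as an open sore. A positive primary result could come mainly from less early redness, with established sores unchanged. A null result could hide fewer open sores beneath a common background of redness. These lead to different clinical messages, and the analyses in {20a} give no between-arm estimate to tell them apart. Describing grade at each time point falls short of the abstract's promise to determine an effect on severity.

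There is also a question of dilution. A mistaken or short-lived stage I call at one inspection is enough to make an event. If such calls are equally likely in both arms, they raise both event rates, narrow the difference somewhat and lower power.

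**Working it through.** **1. The plan's own figure.** Inputs from Sample size {14}: "Given a type I error of 0.05, a power of 0.8"; a control risk of 23%; a 10-point absolute difference, hence 13% under rotation; 5% dropout. The sidedness of the final test is not stated. I take it as two-sided because the interim rule is ("Early stopping criteria will be a predetermined 2-sided").

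Unpooled formula: n = (1.960 + 0.842)² × (0.23×0.77 + 0.13×0.87) / 0.10² = 227.8. Then 227.8 × 1.05 = 239.2, or 227.8 / 0.95 = 239.8. The pooled formula gives 231, then 244 after dropout. The stated "239 subjects per group are estimated to identify a 10% absolute difference" reproduces. With 239 × 0.95 = 227 evaluable per arm, power for 23% v 13% is 79% (pooled normal approximation).

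**2. Which analyses use stage.**

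| Planned analysis | What it uses | Compares arms by stage? |
|---|---|---|
| Mixed logistic | any sore, yes or no | No |
| Mixed Poisson | number of sores | No |
| Modified intention-to-treat | same responses, fewer patients | No |
| Cost-effectiveness | proportion with sores; comfort | No |
| Grade and location | descriptive summary | No estimate or interval |

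This table carries the point and needs no assumption.

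**3. Possible dilution.** The documents give no false-call rate, so f per patient-inspection is **assumed**: equal in both arms and independent between looks. For k looks, q = 1 − (1 − f)^k, and the observed risk is p + (1 − p)q, with p = 0.23 and 0.13 as true risks. The outcome's wording allows k = 3 (any of 12, 24 and 36 h) or k = 1 (the 36 h look only).

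Example, f = 2%, k = 3: q = 1 − 0.98³ = 0.0588. Control: 0.23 + 0.77×0.0588 = 0.275. Rotation: 0.13 + 0.87×0.0588 = 0.181. Difference 9.4 points, power 67%.

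| Looks | f | Points added (control, rotation) | Difference | Power at 227 per arm |
|---|---|---|---|---|
| 3 | 1% | 2.3, 2.6 | 9.7 | 73% |
| 3 | 2% | 4.5, 5.1 | 9.4 | 67% |
| 3 | 3% | 6.7, 7.6 | 9.1 | 61% |
| 1 | 1% | 0.8, 0.9 | 9.9 | 77% |
| 1 | 2% | 1.5, 1.7 | 9.8 | 75% |
| 1 | 3% | 2.3, 2.6 | 9.7 | 73% |

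The difference itself shrinks little. Somewhat more than half of the power loss comes from the higher event rates: at f = 3% and k = 3, raising the mean rate while holding the difference at 10 points takes power from 79% to 69%, and the shrinkage to 9.1 points takes it on to 61%.

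**4. A harsher assumption.** Suppose the 23% already contains false calls, and true sores fall by the same ratio (13/23). With three looks and f = 1, 2 and 3%, the difference becomes 8.7, 7.4 and 6.2 points and power 67, 52 and 38%.

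**The case against.** The strongest reply is that nothing here is an error. Stage I is a pressure sore under the named international classification, and excluding patients who already show the sign is what makes later events new. Both points stand, and the any-stage primary should remain.

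The safeguards also count. Assessors who are trained, tested, blinded and outside patient care limit differential error. A reader might infer that false calls could create a treatment effect with no real sores behind it. The documents do not support that inference: they plan blinded assessment and give no evidence that it fails. What the safeguards leave open is non-differential error. Blinding does not prevent random calls, and the test as described concerns staging sores, not leaving sore-free skin uncalled.

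A reader might also infer that the trial is underpowered. That does not follow. The false-call rate is assumed, three looks is only one reading of the outcome, and the article does not say which stages or what kind of calls the 23% reflects. The figures of 67–38% in particular rest on that unknown.

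Finally, a supporting analysis could be left to a separate analysis plan, and grade tabulated by arm would show something. But the article specifies its sore analyses in detail, names stage as an outcome, promises a conclusion on severity and then confines grade to description. That is a mismatch between aim and analysis within one document.

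**Conclusion.** The concern holds in a limited form. On the text alone, the plan contains no between-arm estimate that separates early redness from established sores, while stating that it will determine an effect on severity. This should be repaired.

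The dilution is possible but unmeasured. With equal and independent false calls of 1–3% per inspection, and 23% and 13% as true risks, power is about 73–61% with three looks or 77–73% with one, and the 10-point difference falls only to 9.7–9.1 or 9.9–9.7. These figures show sensitivity to an assumption; they do not show that 239 per group is wrong on its own inputs.

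It is tempting to go further and let an analysis of confirmed sores, for example stage I seen at two consecutive inspections, decide how the primary result is labelled. The documents do not support that. A detected sore is reported to the physician and may lead to another dressing, less time on NIV or a mask change ({11a}, {11d}). Persistence at the next look is therefore affected by care after detection. It may differ by arm, since one arm alternates masks anyway, and it cannot be observed in patients with no next inspection.

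**What to change.** Keep the any-stage primary outcome. Add to {20a}:

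- One supporting between-arm estimate, by intention to treat, of the proportion of patients with at least one sore of stage II or worse by 36 h, counting unstageable lesions and suspected deep tissue injury, with a 95% confidence interval.
- A statement that it will be reported beside the primary as an estimate of severity, and will not overrule or relabel it.
- If wanted, an exploratory version that also counts stage I at the same location at two consecutive inspections, with the caveats on care after detection and on patients without a next inspection.

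**Cost.** One paragraph and one further estimate. Stage per lesion, location and all inspection times are already collected ({12}, {18a}), so there is no new data collection and no change in sample size.

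**Limits.** The estimate does not restore any power lost in the primary, and few stage II or worse events are likely by 36 h. For illustration only, at an assumed 5% in each arm with 227 patients, the interval's half-width would be 1.96 × √(2 × 0.05 × 0.95 / 227) = 0.040, or 4 points. That is wide next to a 5% risk.

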### Participant timeline {13}

Patients will be screened for eligibility criteria. Consent will be obtained from the patients, if possible, or their legal representative. Thereafter, patients will be randomized into the treatment or control group. After randomization, the skin underneath the mask and the auricle and occipital regions will be inspected to check for any possible pressure sores every 12 h for the following 4 days. Patient status at hospital discharge will also be evaluated (Fig. 2).

